**Site 1 specific analysis***

A comparison between manometry and experimental device parameters will be assessed to gauge prototype V2 accuracy and repeatability.

**Site 1 and 2 analysis**

The manometric parameters (maximum anal sphincter squeeze pressure (mmHg) and mean anal sphincter resting pressure (mmHg)) for the period before treatment would be compared against parameters after treatment. Clinical indicators Vaizey/Wexner faecal incontinence score, faecal incontinence episodes (days/week), frequency of bowel motions & symptoms, and patient’s own view of effectiveness rating will be analysed. Univariate analysis (paired t-test or Wilcoxon) will be used to evaluate manometric parameter changes, while chi square test will be used to compare clinical indicators.

Non-inferiority study analysis described in Section 5.3 will be used to determine if null hypothesis is accepted or rejected.

***
[figure not shown]
***

***Figure 3.*** *Summary of study procedure*

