**3. AIMS/OBJECTIVES/HYPOTHESES**

*Aim*

To compare the treatment efficacy of anorectal biofeedback (clinical indicators and physiological parameters) performed with a novel home-based device with conventional therapy options in patients with functional defecation disorders.

*Faecal incontinence is a heterogeneous condition, there is no single parameter to adequately define or represent an optimal way of assessing clinical outcomes. A range of subjective and physiological measures of bowel function are used as outcomes measures.*

*Site 1 Specific* - A feasibility assessment at Site 1 will evaluate the accuracy and repeatability of the prototype (V2) against anorectal manometry*

1. *Evaluate the capability of experimental device to generate anorectal exercise profiles*
2. *Compare the accuracy of experimental device against anorectal manometry*

*Site 1 and Site 2*

*Subjective primary outcome measures*

1. *Vaizey and Wexner faecal incontinence scores*
2. *Faecal incontinent episodes (days per week)*

*Objective primary outcome measure*

1. *Anal sphincter squeeze pressure (mmHg)*

*Secondary outcome measures*

1. *Anal sphincter resting pressure (mmHg)*
2. *Patient’s own view of effectiveness rating (“worse”, “same”, “improved”, or “cured”) and rating of that change in an ordinal scale of – 5 to + 5*
3. *Frequency of bowel motions and symptoms*
4. *[Experimental device group] Usability interview – 1. Ease of use, 2. Clarity of instructions, 3. Ease of cleaning, 4. Any additional Issues*

Hypotheses

We hypothesised that instrumented home BF therapy with the novel device is as efficacious as clinic-based BF therapy

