**5.3 Data source and Population**

*Study population and size*

The Site 1 feasibility study will be a pilot study involving n=15 (n=20 with 33% dropout) participants per group. This study will evaluate the capability of the experimental device to provide instrumented BF (create distinct BF exercise profiles and is understood by the user) and compare the data against anorectal manometry. This is similar to our previous study [18] but will use the new prototype (V2) and be in a patient population.

The data from this site will not be analysed together with data from Site 2, given the differences in methodology. However, data from Site 1 will be used to improve the statistical analysis plan for Site 2. Currently, the power calculations for Site 2 are based on a previous study [19], but data from Site 1 will be integrated to improve the calculation of sample size and power for Site 2.

Site 2 sample size and power calculations

Based on a previous study of biofeedback treatment for faecal incontinence [19], we estimate that for assessing home-BF and clinic-BF efficacy with a sample size of 30 per group (n=40 with 33% dropout), the paired t-test at the 0.05 significance level can detect a mean change in anorectal function measure of at least 0.45 SD with 0.80 power. This corresponds to at least a mean decrease of 8 in Vaizey/Wexner faecal incontinence score, decrease of 0.6 in faecal incontinence episodes, and 40% increase in anal sphincter squeeze pressure.

For the non-inferiority study, based on changes in the primary outcome measures, with n=30 per study arm, the test for non-inferiority has 0.70 power to reject, at the 0.05 significance level, the null hypothesis that the mean change due to home-BF is smaller than clinic-BF by at least 0.44 SD in favour of he alternative hypothesis that mean changes due to home-BF is no more than 0.44 SD lower than clinic-BF (i.e. Ho: ΔHB-ΔOB<−0.44SD vs. Ha: ΔHB-ΔOB≤−0.44SD).

Using estimates from previous study [19], we consider home-BF no worse than or better than clinic-BF if the home-BF group had at least 9 point decrease in Vaizey/Wexner faecal incontinence score (11 for clinic-BF, SD=3), 0.95 days/week decrease in faecal incontinence episodes (1.1 for clinic-BF, SD=0.25), and 19 mmHg increase in anal sphincter squeeze pressure (25 mmHg for clinic-BF, SD=10).

*Data collection/Outcome measurements*

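### Resting pressure is analysed by a before-versus-after test, so the plan as written gives no home-versus-clinic estimate for this listed secondary outcome

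*Protocol*

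**What the plan says.** Section 3 of the protocol states a comparative aim: "To compare the treatment efficacy of anorectal biofeedback (clinical indicators and physiological parameters) performed with a novel home-based device", set against conventional therapy. The hypothesis is also between arms: "instrumented home BF therapy with the novel device is as efficacious as clinic-based BF therapy". Squeeze pressure is the objective primary outcome, and resting pressure heads the list of secondary outcomes. Section 5.8 randomises participants 1:1 to parallel groups.

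Under Data analyses in Section 5.8 (Site 1 and 2 analysis), the protocol names squeeze and resting pressure together and says that these parameters "for the period before treatment would be compared against parameters after treatment". It then fixes the test: "Univariate analysis (paired t-test or Wilcoxon) will be used to evaluate manometric parameter changes". A chi-square test is assigned to the clinical indicators. The section closes with "Non-inferiority study analysis described in Section 5.3 will be used to determine if null hypothesis is accepted or rejected".

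Section 5.3 defines the scope of that last analysis: "For the non-inferiority study, based on changes in the primary outcome measures". Its worked criteria cover the Vaizey/Wexner score, incontinence episodes and squeeze pressure. It gives no criterion, SD or expected change for resting pressure.

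**The concern.** A paired test of before against after asks whether pressure changed. It does not ask whether the change differed between home and clinic, which is the trial's question. Squeeze pressure has the same paired test but, as a primary outcome, also falls under the between-arm non-inferiority test. Resting pressure does not, so it is the one manometric outcome in Section 3 for which the stated analysis contains no contrast between the randomised arms.

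What is at stake is the comparative reading of that outcome. If the only inferential results are paired tests, they cannot supply it. A significant change in one arm and not in the other does not show that the arms differ, and significance in both does not show that they are alike.

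**Working it through.** **1. Which analyses could reach resting pressure?**

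| Analysis in the protocol | Contrast | Covers resting pressure? |
|---|---|---|
| Paired t-test or Wilcoxon (Section 5.8) | before vs after | yes |
| Chi-square (Section 5.8) | clinical indicators | no, not manometry |
| Non-inferiority test (Sections 5.3 and 5.8) | home vs clinic | no, primary outcomes only |

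No row gives a between-arm result for resting pressure.

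**2. Is the paired test meant within each arm?** Section 5.8 does not say so, but the power statement in Section 5.3 points that way. It gives the paired t-test 0.80 power for a change of 0.45 SD with 30 per group at the 0.05 level.

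- One group of 30: the noncentrality is 0.45 × √30 = 2.465. One-sided 0.05, normal approximation: Φ(2.465 − 1.645) = 0.794, which matches 0.80. The one-sided noncentral t gives 0.777.
- One group of 30, two-sided: 0.693 (normal) or 0.664 (noncentral t).
- Two-sample comparison, 30 vs 30, at 0.45 SD: about 0.40–0.41 two-sided, about 0.54 one-sided.

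The stated figure fits a one-group before-after test of 30. Pooling the two arms in one paired test would give no home-versus-clinic answer either.

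**3. How poorly would paired results stand in for the missing contrast?** Inputs: 30 evaluable per arm and the 0.05 level (Section 5.3). Assumptions: normal changes with equal SD, the same true change in both arms, and effect sizes chosen as a range because the protocol gives none. With p the power of each arm's paired t-test (noncentral t, 29 df), and the arms independent, P(exactly one arm significant) = 2p(1 − p).

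| True change in both arms | p, two-sided | 2p(1 − p) | p, one-sided | 2p(1 − p) |
|---|---|---|---|---|
| 0.30 SD | 0.355 | 0.46 | 0.484 | 0.50 |
| 0.45 SD | 0.664 | 0.45 | 0.777 | 0.35 |
| 0.53 SD | 0.801 | 0.32 | 0.883 | 0.21 |
| 0.60 SD | 0.888 | 0.20 | 0.941 | 0.11 |
| 0.70 SD | 0.959 | 0.08 | 0.982 | 0.04 |

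Both versions are shown because the protocol does not state the sidedness of the paired test. The unrounded two-sided figure at 0.70 SD is 0.078.

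**4. What would a direct comparison deliver?** For a difference in mean change with 30 per arm:

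- 95% half-width = t(0.975, 58) × √(2/30) = 2.002 × 0.258 = 0.52 SD of change.
- Power for a 0.5 SD difference, two-sided 0.05: noncentrality 0.5/0.258 = 1.94, giving about 0.48.
- Smallest difference detectable with 80% power: 0.74 SD.

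These figures are before any gain from baseline adjustment.

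**The case against.** The strongest objection is that this belongs in the statistical analysis plan, which is not shown and which Section 5.3 says will be improved with Site 1 data. The model for one secondary outcome is a usual item for that document, and a before-after summary is a legitimate descriptive step. This would settle the matter if the protocol had left the analysis open. It did not: it names the outcome, the contrast and the test, and the contrast is not the one its aim calls for.

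Other parts of the objection do stand:

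- A reader might infer that the protocol plans two separate within-arm tests and nothing else. It writes neither the word only nor the phrase within each arm. The per-arm reading is an inference from the paired test and from the power statement.
- A reader might also infer that the arms will be judged by setting two p-values side by side. Nothing says so, and the comparative decision is assigned to the non-inferiority analysis. The percentages in the working measure what such a reading would cost; they do not describe a planned step.
- It is tempting to say that a real loss in the home arm would be hidden. With assumed true gains of 0.7 SD at home and 1.2 SD in clinic, both paired tests would be significant in about 96% of trials (0.959 × 1.00). But Section 7.3 foresees reporting descriptive statistics such as mean±SD, which would show the gap if given by arm. The direct comparison would itself have only about 48% power for that 0.5 SD difference.
- Squeeze pressure does have a between-arm test, so the physiological part of the aim is not left without a randomised comparison.

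**Conclusion.** The point holds in limited form. For resting pressure, the protocol fixes a before-versus-after test, and its only between-arm test of change is confined to the primary outcomes. The analysis as written therefore yields no randomised home-versus-clinic estimate for this outcome. The data to produce one are collected in both arms, so the gap lies in the stated analysis and not in the design. The primary conclusion is unaffected.

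That conclusion rests on the text alone. Its size rests on assumptions: with 30 per arm and equal true changes of 0.30 to 0.60 SD, paired tests would disagree between arms in about 20–46% of trials (two-sided) or 11–50% (one-sided), falling below 8% at 0.70 SD. The effect sizes and the sidedness are not given for this outcome, so the range illustrates why paired results are no substitute and does not predict this trial. It is worth correcting, at moderate weight.

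**What to change.** In Section 5.8 (Site 1 and 2 analysis), add that at Site 2 resting pressure is compared between arms as the home-minus-clinic difference in end-of-treatment pressure, adjusted for baseline pressure, with a 95% confidence interval, and that the before-after results are descriptive. A two-sample comparison of changes would also close the gap; adjusting for baseline is usually the more precise choice.

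The cost is a sentence of wording. Manometry before and after therapy is already planned for every participant, so no visit, measurement or participant is added, and the sample size need not change for a secondary outcome. The downside is a wide interval, about ±0.52 SD of change before baseline adjustment. The text should say that the result is an estimate, and that an interval including zero is not evidence of equivalence.

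### Chi-square is the only test named for comparing two numeric primary outcomes; it contradicts Section 5.3's mean-change hypothesis and cannot show non-inferiority

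*Protocol*

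**What the plan says.** Section 3 of the Protocol names as subjective primary outcomes the "Vaizey and Wexner faecal incontinence scores" and incontinent episodes counted in days per week. The objective primary outcome is squeeze pressure in mmHg. All are numeric.

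Section 5.3 plans them on that scale. It gives, for example, a "9 point decrease in Vaizey/Wexner faecal incontinence score (11 for clinic-BF, SD=3" points), with similar figures for days per week and squeeze pressure. It states the Site 2 non-inferiority hypothesis as a difference between arms in mean change, with a limit of 0.44 SD. Separately, it powers a within-group change with a paired t-test.

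In Section 5.8, the Site 1 and 2 analysis defines the indicators: "Clinical indicators Vaizey/Wexner faecal incontinence score, faecal incontinence episodes (days/week), frequency of bowel motions & symptoms, and patient’s own view of effectiveness rating will be analysed". It then assigns the tests: "Univariate analysis (paired t-test or Wilcoxon) will be used to evaluate manometric parameter changes", "while chi square test will be used to compare clinical indicators". The manometric contrast is before against after: values "for the period before treatment would be compared against parameters after treatment". The closing sentence reads: "Non-inferiority study analysis described in Section 5.3 will be used to determine if null hypothesis is accepted or rejected".

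**The concern.** The two sections prescribe incompatible treatments of the same primary outcomes. A chi-square test needs categories, and the Protocol gives none for the score or for days per week. If categories were chosen, the test would look for any difference in proportions. It would carry no margin in points or days, so a non-significant result would not be evidence that home treatment is acceptably close to clinic treatment.

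The hypothesis in Section 3 is that home treatment is as efficacious as clinic treatment, and Section 7.1 says the data will go into a regulatory submission. The only tests named are a chi-square test and a before-after test. An analyst could therefore report a non-significant chi-square, or significant improvement in both arms, as support for that hypothesis. Neither result would support it.

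**Working it through.** **1. The sections side by side**

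| Outcome (all primary, Section 3) | Scale in Section 5.3 | Test named in Section 5.8 |
|---|---|---|
| Vaizey/Wexner score | mean fall 9 home, 11 clinic, SD 3 | chi-square, no cut-off |
| Incontinent days/week | mean fall 0.95 home, 1.1 clinic, SD 0.25 | chi-square, no cut-off |
| Squeeze pressure | mean rise 19 home, 25 clinic, SD 10 mmHg | paired t-test or Wilcoxon, before against after |

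Section 5.3 gives a hypothesis, a power and limits for the between-arm question. The only test it names is the paired t-test.

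**2. The plan's own between-arm figure**

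Section 5.3 states power 0.70 with 30 per arm, 0.44 SD and level 0.05. For a two-sample comparison of mean change with a true difference of zero, power = Φ(0.44/√(2/30) − z) and 0.44/0.258 = 1.704.
- One-sided 0.05: Φ(1.704 − 1.645) = 0.52.
- One-sided 0.025: Φ(1.704 − 1.960) = 0.40.

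The stated 0.70 is not reproduced. That is a separate point. What matters here is that the power statement concerns a difference in mean changes, not in proportions.

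**3. What a non-significant chi-square would mean**

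Inputs from Section 5.3: falls of 11 (clinic) and 9 (home), SD 3, 30 per arm. Assumptions: normal changes, the stated SD is that of the change in each arm, and the Section 5.3 criterion is read as a margin of 2 points. Home treatment is then exactly at the limit. Because the Protocol gives no cut-off, assume that a fall of at least 10 points counts as success.
- Clinic: Φ((11 − 10)/3) = 0.631. Home: Φ((9 − 10)/3) = 0.369. Difference 0.261.
- SE under no difference: √(2 × 0.5 × 0.5/30) = 0.129. SE under these proportions: √(2 × 0.631 × 0.369/30) = 0.125.
- Chance of significance at two-sided 0.05: Φ((0.261 − 1.96 × 0.129)/0.125) ≈ 0.53.

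The chi-square is therefore non-significant in about 47% of such trials. Summing exact binomial probabilities (Pearson test, no continuity correction) gives 46%. Cut-offs from 8 to 12 points give 46% to 54%. A margin-based test at one-sided 0.05 would wrongly declare non-inferiority in 5%.

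Cutting also loses information. A median split of a normal outcome keeps 2/π = 64%, so 30 per arm act like 30 × 0.637 ≈ 19. The median split is likewise an assumption.

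**4. What two significant paired tests would mean**

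Inputs from Section 5.3: clinic rise 25 mmHg, SD 10, 30 per arm. The criterion of 19 mmHg is read as a margin of 25 − 19 = 6 mmHg. Standard error within an arm: 10/√30 = 1.83. Between arms: 10 × √(2/30) = 2.58. Results from 20,000 simulated trials, with non-inferiority tested at one-sided 0.05:

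| True home rise | Home mean/SE | Both paired tests significant | Non-inferiority shown |
|---|---|---|---|
| 19 mmHg (at the limit) | 19/1.83 = 10.4 | about 100% | about 5% |
| 10 mmHg | 10/1.83 = 5.5 | 99.9% | 0% |

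In the second row the expected lower confidence bound is (10 − 25) − 1.67 × 2.58 = −19.3 mmHg, far below −6. Yet both arms improve significantly almost every time.

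**The case against.** The strongest reply is that Section 5.8 does not leave the non-inferiority decision to chi-square or to the paired tests. Its closing sentence sends that decision to Section 5.3, where the contrast is between arms and squeeze pressure is covered with its own figures. Details of the estimator commonly sit in a SAP, which is not shown here, and reporting equivalence from a non-significant chi-square would depart from the written plan.

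Much of this stands, and it rules out three stronger readings that a reader might infer.

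- **No between-arm comparison is planned.** Not supported: the reference to Section 5.3 shows that one is intended. What is missing is a named test.
- **The paired test is an error.** Not supported: Section 5.3 powers a within-group change with a paired t-test, and Section 5.8 follows it. The test is unsuitable only as a basis for non-inferiority, a use the Protocol does not claim.
- **Leaving out baseline adjustment is an error.** Not supported: a randomised comparison of mean changes is valid without it. Any gain in power depends on an assumed correlation and on a test sidedness that Section 5.3 does not state.

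The reply does not rescue the chi-square assignment. The Protocol does not leave that choice open: it names a test that conflicts with its own hypothesis. Following the reference leads to no between-arm test or confidence bound. The null and alternative there are both written on the same side of −0.44 SD. The criteria imply 2/3 = 0.67, 0.15/0.25 = 0.60 and 6/10 = 0.60 SD rather than 0.44.

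**Conclusion.** The concern holds for the chi-square assignment. Two of the numeric primary outcome types are given a test that needs undefined categories and contradicts the mean-change hypothesis in Section 5.3. The reference back to that section shows the right intention but does not supply a replacement test.

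If non-significance were read as non-inferiority, the error rate at the Protocol's own limit for the score would be about 46% to 54%, against 5% for a margin-based test. This range rests on normal changes, the stated SD applying to the change in each arm, 30 evaluable per arm, and assumed cut-offs of 8 to 12 points. The contradiction itself rests on none of these. The paired-test results show only that improvement in both arms is no evidence of non-inferiority; they do not count against using those tests for the within-arm aim.

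**What to change.** Rewrite the Site 1 and 2 analysis in Section 5.8, and Section 5.3 to match:

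- For each numeric primary outcome at Site 2 (Vaizey, Wexner, incontinent days per week, squeeze pressure), replace chi-square or add to the paired test an estimate of the home-minus-clinic difference in mean change with its confidence interval. State the level and sidedness.
- Compare the relevant bound with one margin per outcome, after reconciling 0.44 SD with the criteria of 0.60 to 0.67 SD and correcting the direction of the hypotheses.
- Prefer baseline-adjusted ANCOVA where a baseline is collected: the scores (first and last appointment) and manometry (before and after therapy). This is an efficiency gain, not a correction. For days per week, first confirm that a comparable pre-treatment value exists, because the diary is described as kept during therapy.
- Keep the paired t-test or Wilcoxon for the within-arm aim, and say that it does not bear on non-inferiority.
- Limit chi-square to categorical items such as the patient's four-level rating of effectiveness.

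The cost is Protocol or SAP wording. The scores and manometry need no new data. Days per week may need a short pre-treatment diary if a change from baseline is to be analysed and no comparable value is collected.

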**During biofeedback therapy**

- Participants keep a physical or digital bowel diary (bowel habits, stool consistency, symptoms)
- Participants keep a physical or digital food diary (meals, macro nutrients consumes, fibre consumed)
- The Vaizey and Wexner faecal incontinence score completed at the first and last appointment [20, 21]
- A the last appointment, participant provide self-evaluation of treatment efficacy and change [22]

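### The patient's ordered effectiveness rating is assigned a plain chi-square test, which ignores order and direction and gives up power that an ordered between-arm test would keep.

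*Protocol*

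**What the plan says.** Section 3 of the protocol makes the patient's view of effectiveness a secondary outcome. It has two parts: a four-grade verdict (worse, same, improved, cured) and a "rating of that change in an ordinal scale of – 5 to + 5". Section 5.3, under During biofeedback therapy, collects it at the last appointment only, where "participant provide self-evaluation of treatment efficacy and change". There is no baseline value, so any test of it must compare the arms.

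Section 5.8, under Site 1 and 2 analysis, groups the rating with the Vaizey/Wexner score, incontinence episodes and bowel frequency as clinical indicators: the "patient’s own view of effectiveness rating will be analysed". The next sentence gives the manometric changes a paired t-test or Wilcoxon test, "while chi square test will be used to compare clinical indicators". It mentions no trend version of chi-square, grouping of categories or ordinal model.

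Section 5.3 plans Site 2 on a "sample size of 30 per group (n=40 with 33% dropout") and Site 1 as a "pilot study involving n=15 (n=20 with 33% dropout) participants per group". Its non-inferiority test covers the primary outcomes only, so the rating falls outside it.

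**The concern.** The trial asks whether home biofeedback is as efficacious as clinic biofeedback. For a patient rating, that is a question about level and direction: do home patients place themselves lower on the scale? The Pearson chi-square null is that the two arms have the same distribution over unlabelled categories. It treats a move from +4 to -4 no differently from a move from +4 to +3, and it reports no direction.

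Two things follow. A moderate worsening in the home arm is less likely to be detected than the data allow. And a significant result need not mean that either arm was rated worse. The rating is the patient's overall verdict on the device, so its analysis should be able to speak to that question.

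**Working it through.** **Plan's own figure.** The protocol gives no power or distribution for this comparison, so there is nothing to reproduce. The rating's distribution below is an assumption; the sample sizes and benchmark shifts come from the protocol.

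**Inputs.**
- Analysed patients per arm: 30 at Site 2 and 15 at Site 1 (Section 5.3).
- Benchmark worsening: 0.44 SD, the stated non-inferiority margin. Section 5.3's raw Vaizey/Wexner figures imply (11 - 9)/3 = 0.67 SD. These margins belong to the primary outcomes and serve here only as yardsticks.
- Assumed: clinic ratings normal with mean +2 and SD 2, rounded and clipped to -5 to +5. For the four grades the scale is cut at below 0, 0, 1 to 4, and 5. Two-sided 0.05.

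**Tests.** Chi-square: X² = Σ(O - E)²/E, with E = row total × column total / N and (2 - 1)(k - 1) degrees of freedom. That is 3 for four grades and 10 for eleven points. The rank-sum test (tie-corrected) is directed at whether P(home better) + ½P(tie) departs from ½.

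**Order.** Shuffling the category labels of an example table left chi-square unchanged (X² = 2.835, p = 0.418). The order of the categories does not enter the statistic.

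**Sparsity.** A full 2 × 11 table with 60 patients has a mean expected count of 60/22 = 2.7. In simulation about three quarters of expected counts were below 5.

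**Power at 30 per arm, home arm worse (simulated).**

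| Shift | Four grades: chi-square / rank-sum | Loss | Eleven points: chi-square / rank-sum | Loss |
|---|---|---|---|---|
| 0.44 SD | 0.19 / 0.31 | 0.12 | 0.10 / 0.36 | 0.26 |
| 0.67 SD | 0.41 / 0.60 | 0.19 | 0.25 / 0.70 | 0.45 |
| 0.7 SD | 0.45 / 0.64 | 0.19 | 0.28 / 0.72 | 0.44 |

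At 1.0 SD chi-square power is 0.79 on four grades and 0.59 on eleven points.

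**Sensitivity to the assumed distribution.** At 0.7 SD on eleven points, SD 1.5 gives 0.30 against 0.72 and SD 3 gives 0.28 against 0.72. A separate set of baselines (20,000 trials each) gives, on four grades, 0.19–0.22 against 0.33–0.34 at 0.44 SD and 0.44–0.47 against 0.63–0.65 at 0.67 SD. On eleven points it gives 0.10–0.12 against 0.36, and 0.23–0.27 against 0.69.

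**Site 1, 15 per arm.** Chi-square power on four grades stays below 0.45 even at an odds ratio of 5. For one baseline (10/25/45/20%) it is 0.43 against 0.64 for rank-sum.

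**Spread only: same underlying centre, home ratings more variable, 30 per arm.**

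| SD home vs clinic | Chi-square rejects (eleven points to four grades) |
|---|---|
| 2.5 vs 2 | 5–9% |
| 3 vs 2 | 11–23% |
| 3.5 vs 2 | 19–40% |

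Rank-sum rejects in 4–6% across these settings.

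**The case against.** **Chi-square does not miss most worsening in general.** A reader might infer that it does. At 1.0 SD it detects 0.79 on four grades, and with other baselines it reaches 0.61–0.66 at an odds ratio of 4 and 0.76–0.80 at 5. This stands: the loss is material for moderate shifts, up to roughly 0.7 SD at 30 per arm.

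**Small numbers share the blame.** At 0.44 SD the rank-sum test itself misses 1 - 0.31 = 0.69 of trials on four grades and 1 - 0.36 = 0.64 on eleven points. This also stands: only the difference between the tests is due to the choice of test.

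**The eleven-point figures rest on a reading.** The analysis text names the effectiveness rating, a term that Section 3 attaches to the four grades. The -5 to +5 rating follows as a second item, and no table layout is given. An ungrouped 2 × 11 table is therefore possible but not stated, and the four-grade figures are the more secure. If the grades were collapsed to improved or cured against the rest, chi-square power at 0.7 SD would be about 0.54 against 0.65 for rank-sum on four grades, a loss of about 11 points. An analysis plan that is not shown might add a grouping or a trend test. The protocol, however, already names a plain chi-square, and none of this is in it.

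**Rejection on spread is not a false positive.** The distributions do differ in those scenarios, so the chi-square null is false, and more home patients rating themselves worse may be of clinical interest. Under a true null the test rejected in only 3.5% of trials on eleven points. The valid complaint is narrower: a significant result would not show that either arm was rated lower. With a modest difference in spread the effect is small.

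**The outcome is secondary.** The claim of equal efficacy rests on the non-inferiority analysis of the primary outcomes, so this test neither makes nor breaks it. The same sentence also sends the numeric primary scores to chi-square. That is a weightier matter, and the present point is confined to the ordered rating.

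**Conclusion.** The point holds in a limited form. The protocol calls the rating ordinal and then assigns it a test that ignores order and direction. For a worsening of 0.44 to 0.7 SD with 30 per arm, the cost against a rank-sum test is about 12 to 19 points of power on the four grades, and about 26 to 45 points if the -5 to +5 scale is tabulated ungrouped. A difference in spread alone can produce significance in 5–9% to 19–40% of trials, depending on how large it is.

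These figures rest on an assumed rating distribution. The direction of the loss held across every baseline tried, but its exact size is not known. The documents do not support saying that the test misses most real worsening, that its spread-driven rejections are errors, or that the main efficacy conclusion is at risk. The change is worth making because the outcome is the patient's own verdict and the better analysis uses the same data.

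**What to change.** In Section 5.8, Site 1 and 2 analysis, state that both the four-grade verdict and the -5 to +5 rating are compared between arms with the Wilcoxon rank-sum test or a proportional-odds model. Report the effect with its confidence interval: the probability that a home patient rates better than a clinic patient (ties counted as half), or the odds ratio. Reserve chi-square or Fisher's exact test for binary or unordered items.

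The rank-sum test must be named explicitly. The Wilcoxon test now in that paragraph is paired with the paired t-test for before/after manometric changes and does not cover a comparison of arms.

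The cost is a short text edit. It needs no new data, visits or patients. It will not cure the limited power at small shifts, but the confidence interval will show how much worsening the data leave open.
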